### Process evaluation analysis

The participation rate, numbers of consultations, the direct and indirect time related to each consultation, the kinds of problems presented, completion of intervention according to protocol, and any reasons for non-compliance will be assessed. Ten percent of intervention sessions will be overseen by a senior researcher aiming to evaluate treatment fidelity. The participants in the intervention group will rate their degree of belief that the rehabilitation program will help on a scale from 1 to 10 (worst to best) during sessions 1 and 3. After completion of the intervention, the participants and family members will be asked to evaluate the intervention as well as their satisfaction (acceptability).

### Health economic analysis

To determine the cost-effectiveness if the intervention proves to be effective (i.e., at least a moderate effect size on one of the primary outcomes), a statistical analysis of costs will be performed. The total costs will be calculated by adding up direct health-care costs, direct non-health costs, and indirect costs. As the distribution of costs can be skewed, differences in costs between groups will be calculated by means of bootstrapping. A cost-utility analysis will relate the difference between the intervention and control group to changes in utility. This will result in costs per quality-adjusted life years (QALY). QALYs can be derived from the EQ-5D data. Standard discounting will be performed for both costs and outcomes together with sensitivity and uncertainty analyses to gain insight into the generalizability of the economic evaluation.

#### Interim analyses {21b}

No interim analyses will be conducted.

#### Methods in analysis to handle protocol non-adherence and any statistical methods to handle missing data {20c}

Missing data will be handled by multiple imputations for all analyses except the mixed-model analyses, in which missing data will be handled by the analysis using the maximal likelihood approach under the assumption of missing at random.

### Oversight and monitoring

#### Composition of the coordinating centre and trial steering committee {5d}

The translation and adaptation of the intervention program, as well as monitoring of the research process, were performed in close cooperation with the user organization Norwegian Association of People with Injuries, LTN (https://www.personskadeforbundet.no). The Data Protection Office at OUH has reviewed and accepted the trial and will be consulted for any ethical considerations.

#### Composition of the data monitoring committee and its role and reporting structure {21a}

Because of the small size of the study and the timing of the intervention and follow-ups (4 months’ intervention, assessment at 4–5 months and 12 months), we are documenting each intervention and follow-up by date and time to ensure adherence to protocol. Based on this, an external committee was deemed unnecessary.

### Adverse event reporting and harms {22}

Any adverse events will be registered and reported in future publications.

### Frequency and plans for auditing trial conduct {23}

Not applicable.

### Plans for communicating important protocol amendments to relevant parties (e.g., trial participants, ethics committees) {25}

Important protocol modifications will be reported to the Data Protection Office at OUH and amendments will be made to the trial registry (Clinicaltrials.gov).

### Dissemination plans {31a}

Trial reports and other dissemination documents will be written according to the Consolidated Standards of Reporting Trials (CONSORT) statement to facilitate transparency and critical appraisal of the trial [72]. Authorship criteria will adhere to the International Committee of Medical Journal Editors (ICMJE) recommendations [73]. Publications are planned for journals in the fields of neurology, neuropsychology, and rehabilitation. Results will further be disseminated at relevant conferences, national and international meetings, and expert forums. The results will be shared with the user organization and its members as well as policy makers as part of the renewal of rehabilitation services.

## Discussion

This project is innovative in its focus on rehabilitation goals with subjective and long-term relevance to each patient and in the establishment of close collaboration between different levels of health care. The RCT design will enable the establishment of the efficacy of the intervention and, if effective, include a cost-effectiveness analysis. In addition to replicating the effectiveness of the program found by a previous study within a universal health-care system, it will provide knowledge of the suitability of the intervention in civilians living with more severe TBIs, as well as provide information about the effectiveness of the intervention 8 months following treatment. To our knowledge, this is one of the first studies to use a manualized and individualized approach to rehabilitation intervention in the chronic phase of TBI with standardized outcome measures. Hence, the study might potentially have important implications on treatment options and delivery in the chronic phase of TBI that may inform policy and treatment planning [32]. The in-home rehabilitation approach is individually tailored and not only applicable to a TBI population; thus, the findings of this study will bear relevance to other conditions involving chronic neurological deficits and have innovation potential in establishing new modes of collaboration and knowledge transition between specialized acute and post-acute neurosurgical and rehabilitation facilities and rehabilitation services in the municipalities. Users will be involved in all phases of the project, which is in line with recommendations to include users’ perspectives in the development of treatment strategies [74]. The study will also contribute to increased research collaboration among universities, colleges, and primary-care services in the municipalities.

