**Methods/design:**

This study protocol describes a randomized controlled trial (RCT) aimed at evaluating the effectiveness of a goal-oriented and community-based intervention for increasing community integration, quality of life, and functional independence in the chronic phase of complicated mild to severe TBI. Participants will be recruited from Oslo University Hospital, Norway. Patients aged 18–72 years living at home with MRI/CT-verified intracranial abnormalities, a TBI diagnosis, a time since injury of ≥ 2 years, and who experience either current TBI-related problems or restrictions in community integration will be included. The 120 participants will be randomized 1:1 to either (a) an intervention group, which will receive an in-home intervention program over 4 months, or (b) a control group receiving standard care in the municipalities. The intervention will consist of six home visits and two telephone contacts with a rehabilitation professional. A SMART-goal approach will be adopted to target the individual’s self-reported TBI difficulties in everyday life. Primary outcomes will be self-reported quality of life and participation. Secondary outcomes include symptom burden, emotional functioning, and clinician-assessed global outcome and need for rehabilitation services. Outcomes will be evaluated at baseline and 4–5 and 12 months after baseline. Caregiver burden and general health will be assessed in participating family members. Goal attainment and acceptability will be evaluated in the intervention group. A process evaluation will be carried out to evaluate protocol adherence, and a cost-effectiveness analysis will be applied if the intervention is found to be effective.

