Hence, the current study aims to evaluate an in-home rehabilitation program tailored to the individual’s TBI-related difficulties in the chronic phase. This randomized controlled trial (RCT) was inspired by a home-based rehabilitation study by Winter et al. that included 81 veterans with TBI in a two-group RCT [29]. While the control group received treatment as usual (TAU), the intervention group followed an eight-session, home-based rehabilitation program delivered in the veterans’ homes and in close collaboration with a family member. The intervention was person-centered, focusing on targeted activity problems identified by the veterans, and used an action plan that included goals and tailored strategies to fit the individual’s physical and social environments. Their study documented the efficacy of the in-home program guided by the person–environmental fit model and showed significantly higher community re-integration and less difficulty managing targeted problems in the treatment group, compared with controls. However, since the study only included military veterans with TBI, the authors emphasized the need for replication with civilians. Almost 70% of participants in Winter et al.’s study had mild TBI, and additional investigation is needed in larger populations, including individuals with moderate-to-severe TBI. Furthermore, the Winter et al. study did not include long-term follow-up or process or cost-effectiveness evaluations. Finally, health-care delivery and social-security systems, as well as culture, differ between countries. For instance, Norway is a welfare state with a public health-care system and may not be comparable to the US veteran system. Hence, the study protocol by Winter et al. was adapted according to cultural issues and differences in the target population. The aim of the current study is to evaluate a community-based, individualized, and goal-oriented intervention targeting civilians with complicated mild to severe TBI in Norway.

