### Eligibility criteria {10}

The study will include patients from OUH with a TBI diagnosis and CT/MRI-verified intracranial abnormalities. Participants must be 18–72 years of age at inclusion, ≥ 16 years of age at the time of the injury, at least 2 years’ post-injury at study inclusion, and living at home. The participants must report ongoing TBI-related cognitive, emotional, and/or physical problems, and/or reduced physical and mental health, and/or difficulties with participation in activities with family, friends, and/or in the community (based on interview and the standardized questionnaires at baseline). If the participants have a family member or friend closely involved in their lives, the family member/friend will be asked to participate as well. Participants with severe progressive neurologic disorders or severe psychiatric disorders that would confound outcome assessments will be excluded as well as those unable to provide informed consent or participate in a goal-setting process. Participants with insufficient fluency in Norwegian to allow for communication with therapists and outcome assessors or that have active substance abuse or violent tendencies that would put therapists at risk during home visits will also be excluded.

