### Patient characteristics

The following sociodemographic variables will be recorded at baseline: age, gender, marital status, living arrangement, educational level, and current employment status. Medical variables will be obtained from the medical journal and include comorbidity, injury characteristics, and clinical severity (Glasgow Coma Scale Score, length of posttraumatic amnesia), neuroimaging results, and primary rehabilitation services received. A neuropsychological test battery will be conducted at baseline (T1) to assess cognitive functioning and guide intervention strategies. The battery consists of tests of abstract reasoning (Similarities and Matrix Reasoning from the Wechsler Adult Intelligence Scale (WAIS-IV) [38]), verbal learning and memory (California Verbal Learning Test-II [39]), and attention span (Digit Span, WAIS-IV [40]) as well as processing speed, mental flexibility, and inhibition (Trail Making Tests and Color Word Interference Tests from the Delis-Kaplan Executive Function System (D-KEFS) [41]). A questionnaire regarding executive functioning in everyday living will also be administered at T1 (the Behavior Rating Inventory of Executive Function Adult Version (BRIEF-A) Self-Report [42]).

If inclusion of a family member is possible, participants will answer a short questionnaire pertaining to the quality of their relationship with their family member (adapted version of the Quality of Relationship scale used by Winter et al. [29]) and the family member will be asked to fill out the BRIEF-A Informant Form [42].

Careful consideration has been given to the selection of neuropsychological tests and questionnaires included for patient characteristics in relation to patient burden, and order of administration will be standardized and checked for missing data during administration.

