### Assignment of interventions: allocation

#### Sequence generation {16a}

Participants will be randomly allocated in a 1:1 ratio to either group. A web-based block randomization will be generated by an independent statistician prior to trial start-up to ensure randomization and complete allocation concealment. Variable block size (generated by Stata version 15) will be applied.

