#### Methods for additional analyses (e.g., subgroup analyses) {20b}

Individual and treatment-related predictors for goal attainment will be assessed by multivariable regression analysis in the intervention group. Intention-to-treat analyses will be performed in all analyses adjusted for sociodemographic and service-content variables from the ICSO-R.

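### The trial says it will inform use in more severe TBI, but the stated analysis gives only a pooled effect and leaves injury severity out of its adjustment set

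*Protocol article*

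**What the plan says.** **Motivation.** The Rationale describes an earlier home-based trial in veterans, almost 70% of whom "had mild TBI, and additional investigation is needed in larger populations, including individuals with moderate-to-severe TBI". The Discussion of the protocol article then says of the present trial that "it will provide knowledge of the suitability of the intervention in civilians living with more severe TBIs".

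**Population.** The abstract places the trial "in the chronic phase of complicated mild to severe TBI". Under Eligibility criteria {10}: "The study will include patients from OUH with a TBI diagnosis and CT/MRI-verified intracranial abnormalities". No GCS or amnesia threshold, minimum number or cap is stated.

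**Severity data.** Patient characteristics lists, among the medical variables, "clinical severity (Glasgow Coma Scale Score, length of posttraumatic amnesia").

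**Allocation.** Sequence generation {16a}: "Participants will be randomly allocated in a 1:1 ratio to either group", in blocks of variable size, with no stratification factor named.

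**Analysis.** The mixed models in {20a} have time and time-by-treatment as fixed effects, and the comparison of interest is at T3. Section {20b} says that all analyses are intention-to-treat and "adjusted for sociodemographic and service-content variables from the ICSO-R". It names no analysis by severity.

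**The concern.** Severity is the feature that separates this trial from the one it builds on. The article says that the trial will be informative about more severe injury, yet its analysis sections contain nothing that yields an estimate for those patients. The severity mix is whatever recruitment delivers, the effect is averaged over that mix, and the adjustment set leaves severity out.

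What is at stake is how the result is read. Suppose the pooled result is positive and complicated mild injuries turn out to be common in the sample. Following the Discussion, readers and policy makers could take it as evidence for moderate and severe TBI. The trial would not have shown that separately, although the variables needed to examine it are on file.

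**Working it through.** **1. The plan's own figure.** Inputs from Sample size {14}: two-sided t-test, alpha 0.025, power 0.80, QOLIBRI difference 12 with SD 20, PART-O difference 1.8 with SD 3. Both give d = 12/20 = 1.8/3 = 0.6. The noncentral t calculation gives n = 54.08 per group, with power 0.799 at n = 54. Then 54/0.90 = 60 randomised per arm. The stated 54 and 60 reproduce, and they are for the overall comparison only.

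**2. What is left for a moderate-severe group.** The article does not give the share with moderate-severe injury. I assume 30%, 50% and 70%; 30% mirrors the earlier trial. Evaluable n per arm = 54 × share, rounded.

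Half-width of the 97.5% interval = t(0.9875; 2n − 2) × 20 × √(2/n):

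| Share (assumed) | n per arm | t | SE | Half-width, QOLIBRI points | Power for d = 0.6 at alpha 0.025 |
|---|---|---|---|---|---|
| All patients | 54 | 2.274 | 3.85 | 8.8 | 0.80 |
| 70% | 38 | 2.288 | 4.59 | 10.5 | 0.63 |
| 50% | 27 | 2.308 | 5.44 | 12.6 | 0.46 |
| 30% | 16 | 2.360 | 7.07 | 16.7 | 0.27 |

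The target difference is 12 points. These widths use the unadjusted t-test on which the plan is sized. Because T1 is in the mixed model, they shrink by √(1 − r²). For an assumed T1–T3 correlation r of 0.4 to 0.7 the factor is 0.917 to 0.714, giving 11.5 to 9.0 points at a 50% share and 15.3 to 11.9 at 30%.

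**3. Testing whether the effect differs by severity.** For share s, the SE of the difference between the two group effects, in SD units, is √(2/(54s) + 2/(54(1 − s))). At s = 0.5 this is √(2/27 + 2/27) = 0.385, and power for a difference of 0.6 SD is Φ(0.6/0.385 − 2.241) = 0.25. At s = 0.3 or 0.7 the SE is 0.420 and power is 0.21. A severity analysis can therefore be descriptive only.

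**4. Chance imbalance between arms.** With 60 v 60 and K moderate-severe patients among 120 (hypergeometric, K = 36, 60, 84), the arms differ in that share by 10 percentage points or more with probability 0.32, 0.36 and 0.32. They differ by 20 points or more with probability 0.03, 0.04 and 0.03.

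**5. What a severity covariate gains.** Assume severity groups differ by 0.2 to 0.8 SD at both T1 and T3, with r = 0.4 to 0.7. Adding severity to a model that already uses T1 then cuts the SE of the T3 difference by about 0.1% to 4%.

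**The case against.** Several points on the other side are sound.

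- **The imaging requirement is a severity floor.** A reader might infer that eligibility has no severity criterion. That is not so: mild TBI without an intracranial abnormality cannot enter. The phrase more severe is relative to the earlier trial, so eligibility secures part of the promise. It does not secure any number with moderate or severe injury.
- **Suitability is a weaker word than efficacy.** No hypothesis from H1 to H6 concerns severity. Acceptability, completion and goal attainment bear on suitability, and the feasibility study was in six people with severe TBI. This stands, and it rules out reading the Discussion as a claim of a powered subgroup result. But no process or acceptability analysis is stated by severity either. The planned regression on predictors of goal attainment could include severity, but it is confined to the intervention arm and cannot estimate a treatment effect.
- **There is baseline adjustment.** A reader might infer that there is none. Section {20b} adjusts for sociodemographic and service variables, and T1 is in the mixed model. Only injury severity is unnamed.
- **Chance imbalance is not bias.** One might infer from the one-in-three chance of a 10-point imbalance that the comparison is at risk. It is not: randomisation keeps the comparison unbiased and the interval already reflects such chance. As an illustration, with an assumed severity gap of 0.5 SD (10 QOLIBRI points), a 10-point imbalance moves the estimate by 0.10 × 10 = 1 point, against an SE of 3.85.
- **Covariates and subgroups are often left to a fuller document.** This is true in general. Here, though, the article itself fixes an adjustment set for all analyses and itself makes the statement about more severe TBI.

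**Conclusion.** The point holds as a limit on what the result can be said to show. As stated, the plan yields one pooled effect. That effect cannot by itself support a statement about moderate-severe TBI, because nothing fixes how many such patients enter and no estimate for them is named. Omitting severity from the adjustment set is a small, avoidable loss.

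The pooled primary comparison is valid, and the sample size of 54 and 60 per arm is correct for it. The documents also do not support the inference that the sample will be mostly mild, since they do not give the severity mix. The widths of about 13 and 17 QOLIBRI points rest on assumed shares of 50% and 30%, on the plan's SD of 20 and on 54 evaluable per arm, without the gain from T1.

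**What to change.** 1. In {20a} and {20b}, add baseline injury severity to the adjustment covariates of the primary mixed models: complicated mild v moderate-severe, from GCS, or from amnesia length where GCS is missing.
2. State that the T3 treatment difference will be reported with its 97.5% interval in each severity group for both primary outcomes, as a pre-specified, non-confirmatory estimate.
3. Limit the Discussion statement on more severe TBI to what that estimate supports.

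The cost is wording only: both variables are already collected and the sample stays at 120. The severity-specific intervals will be wide, some old injuries may need the amnesia-length fallback, and the precision gained from the covariate is small. Stratified blocks are not proposed, because the list was to be generated before start-up and recruitment began in June 2018.

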### Limitations

The protocol has several limitations. The individualized nature of the intervention will make it challenging to compare across participants. As previously discussed, however, individualizing the treatment based on the participant’s own goals and competency is a major strength, as it enhances motivation and ensures delivery of relevant treatment. Using the combination of target outcomes, SMART goals, and GAS further enables statistical comparisons across individualized outcomes. Blinding of therapists and participants will not be possible in this study, but outcome assessors and researchers conducting the statistical analyses will remain blinded to group allocation. A further limitation is that all main outcome measures are self-report measurements, which may pose a problem in cases of reduced self-awareness (an issue in all TBI research). However, GAS will be included as a secondary outcome measure in the intervention group, and inclusion of family members when possible will ensure comparable data to assess self-awareness. In addition, the follow-up period of 12 months includes a risk of drop-out. The therapists will be flexible with the timing of interventions and assessments to prevent participants from withdrawing from the study. In the Winter et al. study, dropouts were mainly seen in the participating family members, and a more flexible approach to family member involvement has therefore been adopted in the current study. Further, dropouts will be evaluated as part of the process evaluation.

## Trial status

Protocol version 3.0. Recruitment for the RCT began in June 2018 and will continue until target sample size has been reached, estimated by the end of 2020.

## Data Availability

Not applicable.

## Abbreviations

BRIEF-A: Behavior Rating Inventory of Executive Function Adult Version
CONSORT: Consolidated Standards of Reporting Trials
CT: Computed tomography
CVLT: California Verbal Learning Test
D-KEFS: Delis-Kaplan Executive Function Systems
GAD-7: Generalized Anxiety Disorder seven-item scale
GAS: Goal Attainment Scaling
GOS-E: Glasgow Outcome Scale-Extended
ICMJE: International Committee of Medical Journal Editors
ICSO-R: International Classification System for Service Organization in Health-related Rehabilitation
MRI: Magnetic resonance imaging
NPCS: Needs and Provision Complexity Scale
OUH: Oslo University Hospital
PART-O: Participation Assessment with Recombined Tools-Objective
PHQ-9: Patient Health Questionnaire-9
QALY: Quality-adjusted life years
RCT: Randomized controlled trial
REK: Regional Ethics Committee
RPQ: Rivermead Post-concussion Questionnaire
SPIRIT: Standard Protocol Items: Recommendations for Interventional Trials
TAU: Treatment as usual
TBI: Traumatic brain injury
WAIS-IV: Weschler Adult Intelligence Scale-fourth edition
